### Data collection

The participants with hip and/or knee OA will be asked to complete electronic questionnaires via a link sent by email. If a participant has no email address or internet access or is reluctant to reply electronically, the questionnaire and a prepaid envelope will be mailed to the participant. Information on participant age, gender, joint replacements, and comorbidity will be collected by the project coordinators during the telephone screening. Other participant characteristics and OA disease related information will be self-reported at baseline (body height, marital status, years of education, occupational status, joints with OA, most affected joint, years with OA diagnosis, and function (Knee injury and Osteoarthritis Outcome Score/ Hip disability and Osteoarthritis Outcome Score ADL subscale)). Demographic data on the GPs and PTs will be collected at the workshop (age, gender, years since graduation, speciality, type of practice, number of GPs/PTs in the practice, number of weekly working hours, and number of people on the GPs’ lists).

### National register data

We will apply for permission to extract data on prescription of medication, sick leave, secondary health care utilization, and total joint surgery from national registers (i.e. The Norwegian Prescription Database, the register of The Norwegian Labour and Welfare Administration, The Norwegian Patient Register, The Norwegian Arthroplasty Register) to merge with collected data after the study has ended. Consent to data merging will be obtained from the participants with hip and/or knee OA.

### Cost-utility

Based on the findings in this study, two economic evaluations will be conducted, applying both health system and societal perspectives. Costs in the health care sector comprise intervention costs and costs related to treatment or assessments, while societal costs include production loss, as well as costs for the individuals and the family. The primary economic evaluation will be cost-utility analysis (CUA) of the incremental cost per quality adjusted life years (QALYs) gained, which will be calculated using the EQ-5D scores at baseline, 3, 6, 9 and 12 months. The secondary evaluation will be a cost-effectiveness analysis (CEA) based on a disease-specific measure of function: Knee injury and Osteoarthritis Outcome Score OoL subscale [44]/ Hip disability and Osteoarthritis Outcome Score OoL subscale [45] (K/HOOS). Incremental cost per K/HOOS will be calculated as the ratio of the difference between groups in mean cost to the difference in mean K/HOOS. By means of bootstrapping, cost-effectiveness acceptability curves (CEACs) will be used to consider the uncertainty surrounding the cost-effectiveness of the integrated OA care model by plotting the probability that the model is cost-effective according to a range of willingness-to-pay thresholds.

### Statistical analyses

Baseline characteristics of the participants with OA, the GPs, and the PTs will be presented for the total study and stratified by cluster. Participant characteristics will also be presented stratified by group allocation. The primary effect analysis will be performed on an intention to treat basis by comparing OA QI summary pass rate in the control group vs. the intervention group with the 6-month follow-up as the primary evaluation time point. Multilevel mixed-models will be fitted to adjust for the effect of clustering (municipality), participant (patient), and repeated measures over time. Analyses of effect and process outcomes in regression analyses will include the baseline value of the outcome variable and be adjusted for covariates at the individual patient participant level (age, gender, education level, pain (NRS 0–10), BMI, baseline function (K/HOOS ADL), self-reported comorbidity). To adjust for potential differences related to GPs behaviour, we will include attendance at the GP workshop as a covariate in analyses. A CACE analysis will be performed to provide an unbiased estimate of treatment effect for participants treated as per protocol specification (in the intervention group: participants having attended the OA patient education programme and performed an exercise programme for at least 8 weeks).

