## Methods/design

### Study design

In order to implement the model and to assess the effects of the tailored strategy, a stepped wedge cluster randomized controlled trial will be conducted [41]. The GPs and the PTs in the six participating municipalities (clusters) in Øvre Romerike will switch from control (current OA care) to intervention (implementation of the SAMBA model for integrated OA care) phase in a randomized order. All municipalities start the trial simultaneously and act as controls until the point in time they are randomized to crossover from the control to the intervention phase, and all municipalities have implemented the SAMBA model for OA care by the end of the inclusion period (Fig. 1).

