**Fig. 1 Fig1:**
[figure not shown]
Timeline for the SAMBA project. *Dark cells represent intervention periods, and blank cells represent control periods. The inclusion of patients will start on January 15^th^ 2015 and end on June 15^th^ 2016. The last six month follow-up will be in December 2016 and the last 12-month follow-up will be in June 2017. ^#^The 6 municipalities will switch from control phase to intervention phase in a randomized order

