### Randomization and blinding

The municipalities will be randomly allocated to one of the six sequences for time of crossover from control to intervention (implementation) phase using a computer-generated list of random numbers. Since the number of inhabitants in the six municipalities varies, stratification on the number of inhabitants less than versus more than 20,000 will be performed to ensure a mix of municipality sizes in the randomized sequence. The allocation sequence will be provided by a statistician. Due to the nature of the implementation strategy, it is not possible to blind the involved GPs and PTs, but the research coordinator performing the telephone interviews will remain blinded. Statistical analyses of primary and secondary outcomes will be performed by the primary investigator and the statistician blinded for group allocation.

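### The primary model as written has no calendar-time term, so in this one-way stepped wedge a background trend in OA care would be partly counted as intervention effect

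*Protocol article*

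**What the plan says.** The Study design section sets up a one-way crossover: "All municipalities start the trial simultaneously and act as controls until the point in time they are randomized to crossover". All six municipalities have the intervention by the end of inclusion. The Randomization and blinding section adds: "The municipalities will be randomly allocated to one of the six sequences for time of crossover from control to intervention (implementation) phase". According to the legend of Fig. 1, inclusion runs from 15 January 2015 to 15 June 2016, which is 17 months.

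The Statistical analyses section gives the primary analysis as "comparing OA QI summary pass rate in the control group vs. the intervention group with the 6-month follow-up as the primary evaluation time point". The model is described as follows: "Multilevel mixed-models will be fitted to adjust for the effect of clustering (municipality), participant (patient), and repeated measures over time". The regression analyses "will include the baseline value of the outcome variable and be adjusted for covariates at the individual patient participant level", and the list is "age, gender, education level, pain (NRS 0–10), BMI, baseline function (K/HOOS ADL), self-reported comorbidity". Attendance at the GP workshop is the last covariate named. Calendar period, step and date of recruitment do not appear.

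Table 3 shows what time means for the repeated measures. The questionnaires fall at 0, 3, 6, 9 and 12, and the footnote defines these as months from the patient's baseline assessment.

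**The concern.** In a stepped wedge, exposure and calendar date are tied together: early recruits are mostly controls and late recruits mostly intervention patients. Randomising the order of crossover protects the comparison only if the analysis conditions on calendar time. A follow-up-month term cannot do this. A patient recruited in February 2015 and one recruited in May 2016 have the same value at the 6-month assessment.

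The protocol itself mentions possible sources of change over the recruitment period. The Background describes a health sector reform that places OA care in primary care, and the recruitment section foresees newspaper articles and waiting-room posters about the study. If patient-reported quality of care rises for such reasons, part of the rise would be credited to the SAMBA strategy in the primary estimate, its interval and its p-value. The same holds for secondary outcomes that compare the two groups, such as referrals to physiotherapy and MRI.

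**Working it through.** **1. The plan's own sample size.** Inputs from Sample size calculations: difference 10, SD 24, two-sided alpha 0.05, power 80%, ICC 0.01, 50 per cluster, drop-out 30%.

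- Per group before inflation: 2 × (24 × (1.96 + 0.84) / 10)² = 90.4, rounded up to 91.
- Design effect: 1 + (50 − 1) × 0.01 = 1.49.
- 91 × 1.49 / 0.70 = 193.7, so 194 per group and 388 in total.

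The stated figure reproduces. It is a parallel-cluster calculation with no period term. Completers: 388 × 0.70 = 272.

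**2. Assumed layout.** Fig. 1 is not reproduced in the text available, so I assume seven equal periods, one municipality crossing at each step, uniform accrual, equal cluster-period sizes, different patients in each period and no covariates.

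**3. Gap in recruitment date.** Switch times are t = 17i/7 months, i = 1 to 6, with sum 51.

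- Mean control entry: Σ(t²/2) / Σt = 268.4 / 51 = 5.3 months.
- Mean intervention entry, by symmetry: 17 − 5.3 = 11.7 months.
- Intervention patients therefore enter about 6.5 months later.

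**4. Model without calendar time** (random municipality intercept, generalised least squares).

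- Cell size: 272 / 42 = 6.48.
- Cell variance: σ² = 0.99 × 576 / 6.48 = 88.05. Municipality variance: τ² = 0.01 × 576 = 5.76. σ² + 7τ² = 128.4.
- Treated periods per cluster are 1 to 6 (sum 21, sum of squares 91). Within-cluster sum of squares of exposure: 21 − 91/7 = 8. Between-cluster: 91/7 − 21²/42 = 2.5.
- Information: 8/88.05 + 2.5/128.4 = 0.1103, so SE = 3.01.
- Within-cluster cross-product of exposure and period: Σu(7 − u)/2 for u = 1 to 6, which is 28. The between-cluster part is zero.
- Bias per one-point-per-period trend: (28/88.05) / 0.1103 = 2.88. As a share of the drift over all seven periods (17 months): 2.88/7 = 0.41. Over ICC 0 to 0.05 and 272 to 388 analysed, the share is 0.38 to 0.47.

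**5. Consequence with no true effect.** Type I error = P(|Z + bias/3.01| > 1.96). The documents give no trend, so the drifts are assumptions.

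| Assumed 17-month drift | Bias | Type I error |
|---|---|---|
| 2 points | 0.8 | about 6% |
| 5 points | 2.1 | about 10% |
| 10 points | 4.1 | about 28% |

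**6. Model with fixed period effects.** The bias from a common trend is zero. The variance is 6σ²(σ² + 7τ²) / [(6×21 − 91)σ² + (21² + 6×7×21 − 7×91 − 6×91)τ²] = 6 × 88.05 × 128.4 / (35 × 88.05 + 140 × 5.76) = 17.4, so SE = 4.18. Power for 10 units, Φ(10/SE − 1.96), falls from 91% to 67% with 272 completers. It is 80% if all 388 are analysed (SE 3.57).

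**The case against.** The strongest reply is that this is one paragraph of a journal article, that it does not claim to give the whole model, and that its covariate list is confined to patient-level variables, where a design term such as period would not belong. It is true that nothing says time will be left unadjusted, and a fuller analysis plan may include it. But the paragraph names the clustering levels, the baseline outcome, seven covariates and a GP-level covariate. An analyst who follows it as written would fit a model without the term that this design depends on. That is more than missing detail.

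A second reply is that the figures ignore the planned baseline adjustment, and this stands. If drift affects baseline and follow-up equally and their correlation is r, about (1 − r) of the bias remains and the SE shrinks by √(1 − r²). For assumed r of 0.3 to 0.7, type I error is about 6–8% for a 5-point drift and 9–17% for a 10-point drift. Drift that arises after baseline is not removed, however. The baseline questionnaire also follows the GP consultation, and the protocol itself says it may be used to assess the effect of that consultation, so the baseline value may already carry intervention effect.

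Three stronger readings may tempt a reader, and the documents do not support them:

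- That all of a secular change would be counted as effect. Under the assumed layout it is about 40% of a linear drift.
- That the smaller standard error is wrong in any case. If there is no time effect, 3.0 is valid under the assumed model.
- That the economic evaluation has the same fault. It says "Incremental cost per K/HOOS will be calculated as the ratio of the difference between groups in mean cost to the difference in mean K/HOOS", which defines a ratio and does not say whether the differences are adjusted.

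A 10-point background rise would also equal the whole target effect, so it is an upper illustration. Growth of Healthy Living Centres is a weak local cause, since the recruitment section already counts one in each of the six municipalities.

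**Conclusion.** The point holds in this form: the model as stated does not condition on calendar time, the design makes exposure depend on calendar time, and a background trend would therefore bias the effect estimate in part. The absorbed share of about 0.41 rests on the assumed layout and on no covariate adjustment. The bias and type I error figures rest in addition on assumed drift sizes, and they are upper figures to the extent that baseline adjustment removes drift already present at enrolment. What does not depend on these assumptions is the direction of the fault and the fact that none of the listed terms represents calendar time. Since it touches the primary estimate, it should be corrected before analysis.

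**What to change.** Add calendar period of recruitment as a fixed effect to the primary model, as step categories or as a smooth calendar-time term if cells are thin, alongside the municipality and patient terms. Do the same in the secondary outcome models that compare the two groups. State in the Cost-utility section that the incremental cost and effect differences are adjusted in the same way.

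No new data collection is needed, because the timing of recruitment is inherent in the trial's records. By the Trial status section data collection was still under way in October 2015, and the last 6-month follow-up was due in December 2016, so the term could be fixed before the primary analysis.

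The cost is precision. Under the assumptions above the standard error rises from about 3.0 to 4.2, and power for 10 units with 272 completers is about 67%, before any gain from covariates or repeated measures. The stated 80% should be recomputed for the stepped wedge analysis, using the actual step dates and expected cluster sizes, and restated.

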### Recruitment of GPs and PTs

GPs and PTs working in private institutes or at FLSs will be invited during outreach visits to each practice and clinic. We aim to recruit 26 (30 %) of the GPs (currently 80 GPs), all PTs (currently 8) at the six FLSs, and 35 (50 %) of the PTs in private practice (currently 70 PTs). In order to facilitate a high attendance among the GPs, the project group will preferably use one of the regular, established meetings in each municipality for the workshop.

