### Sample size calculations

Previous research in the ‘Musculoskeletal pain in Ullensaker Study’ showed that about 12 % of the adult population self-reported OA in their hip and/or knee joints. Among these, 89 % visited their GPs in the previous year. The estimated adult population (aged 40–70) in the six municipalities in Øvre Romerike is about 35 000, of which about 4200 might have hip and/or knee OA and 3700 might visit their GP during a 1-year period. Based on results from a study in 2012 among 1052 members of the Norwegian Rheumatism Association with hip and/or knee OA, we have estimated the intraclass correlation coefficient (ICC) (using the 19 counties as clusters) to be <0.01. Further, we have estimated that a minimum of 194 individuals in each group among the six clusters with an average of 50 individuals per cluster, achieves 80 % power to detect a 10-unit difference between the group means of the primary outcome measure (OsteoArthritis Quality Indicator questionnaire); when the standard deviation for the primary outcome measure is 24 units, the drop-out rate is 30 %, and the intraclass correlation is 0.01, using a two-sided test with a significance level of 0.05. Hence, we aim to include at least 388 individuals in total.

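### The primary mixed model has no GP level, so its standard error can be too small if GPs recruit unevenly across phases or respond differently to the intervention

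*Protocol article*

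**What the plan says.** Under Statistical analyses, the protocol article names the levels of the primary model: "Multilevel mixed-models will be fitted to adjust for the effect of clustering (municipality), participant (patient), and repeated measures over time". The next sentences add the baseline value of the outcome and patient-level covariates. The GP enters once: "To adjust for potential differences related to GPs behaviour", workshop attendance is included as a covariate.

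The GP's part in the trial is described elsewhere:
- Recruitment of participants: GPs identify eligible patients and pass their details to the project group.
- The intervention phase: the first and last steps of the model are GP consultations.
- The GP workshop training package: GPs are trained.
- Recruitment of GPs and PTs: "We aim to recruit 26 (30 %) of the GPs (currently 80 GPs").

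Municipalities are randomised (Randomization and blinding), and GPs change phase with their municipality (Study design).

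The only correlation estimate is under Sample size calculations: "we have estimated the intraclass correlation coefficient (ICC) (using the 19 counties as clusters) to be <0.01". It comes from members of a patient association.

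**The concern.** The outcome partly measures what the GP does. The section on the primary outcome says that the baseline score may reflect the effect of the GP consultation. Patients of the same GP can therefore be expected to resemble one another, and a county-level ICC gives no information on how much. A fixed covariate for workshop attendance shifts the mean for groups of GPs. It does not represent the remaining correlation among patients of one GP.

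If that correlation matters for the phase contrast, the model counts GP variation as independent patient noise. The confidence interval for the primary effect is then too narrow and the p-value too small.

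Two features of the plan make this possible. Table 1 gives GPs outreach visits, reminder calls and newsletters with recruitment feedback, so the mix of recruiting GPs may change after crossover. Workshop attendance is recorded because it will vary, so GPs may also differ in how they respond.

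**Working it through.** **Inputs from the article.** "achieves 80 % power to detect a 10-unit difference between the group means of the primary outcome measure"; "when the standard deviation for the primary outcome measure is 24 units"; "the drop-out rate is 30"%; "using a two-sided test with a significance level of 0.05"; ICC 0.01; average cluster size 50; 388 patients in total; target of 26 GPs.

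**The plan's own figure.**
- Unadjusted: n = 2(1.960 + 0.842)² × 24² / 10² = 90.4, so 91 per group.
- Design effect: 1 + (50 − 1) × 0.01 = 1.49, and 91 × 1.49 = 135.6.
- Drop-out: 135.6 / 0.70 = 193.7, so 194 per group and 388 in total. This reproduces exactly, with clustering counted at one level only.

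**Patients per GP, if the target of 26 is met.** 388 / 26 = 14.9 enrolled. 388 × 0.70 ≈ 272 analysed, and 272 / 26 ≈ 10.5 per GP.

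**Why it depends on recruitment and response.** Suppose GP g contributes n₁g of N₁ intervention patients and n₀g of N₀ control patients.
- A stable GP effect with variance σ² adds σ² Σ(n₁g/N₁ − n₀g/N₀)² to the variance of the phase contrast. This is zero when every GP recruits the same share in both phases.
- An effect drawn separately in each phase, with variance τ², adds τ² Σ[(n₁g/N₁)² + (n₀g/N₀)²]. This never cancels.

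**Hand check of the second case.** Assume 136 analysed per phase, equal GP shares, total variance 576, a wholly phase-specific GP effect, and no municipality or period terms.
- GP ICC 0.10: true variance = 518.4 × 2/136 + 57.6 × 2/26 = 7.62 + 4.43 = 12.05. A model without GP gives 576 × 2/136 = 8.47. The SE ratio is √(8.47/12.05) = 0.84, so the test rejects when |Z| > 1.96 × 0.84 = 1.64, about 10% of the time.
- GP ICC 0.05: true variance = 8.05 + 2.22 = 10.26, SE ratio 0.91, rejection about 7.5%.

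**Null simulation of the stepped wedge.** Assumed: 6 municipalities, 26 GPs nested in them, 7 periods, 272 analysed, SD 24, municipality ICC 0.01, one outcome per patient, no baseline covariate, REML with a Wald z test, 1,200 to 1,500 runs per cell. Monte Carlo error is about 0.006 to 0.010. Type I error:

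| GP recruitment and effect | GP ICC | No GP level, period terms | No GP level, no period terms | GP intercept, period terms |
|---|---|---|---|---|
| Both phases, stable effect | 0 | 0.063 | 0.065 | 0.061 |
| | 0.05 | 0.079 | 0.067 | 0.065 |
| | 0.10 | 0.079 | 0.063 | 0.068 |
| Three-period window, stable effect | 0 | 0.068 | 0.064 | 0.062 |
| | 0.05 | 0.093 | 0.106 | 0.070 |
| | 0.10 | 0.108 | 0.131 | 0.064 |
| Effect differs by phase | 0 | 0.066 | 0.050 | 0.068 |
| | 0.05 | 0.083 | 0.104 | 0.083 |
| | 0.10 | 0.102 | 0.148 | 0.098 |

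At GP ICC 0.10 with recruitment windows, the mean model SE was 4.58 against an empirical SD of 5.46 with period terms (ratio 0.84), and 3.44 against 4.60 without (0.75).

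**Adding the planned baseline covariate.**
- 1,500 runs, baseline-follow-up correlation 0.5, the same GP effect at both times, GP ICC 0.10 with half of it phase-specific: rejection without a GP level was 0.082-0.105 unadjusted and 0.055-0.070 adjusted.
- A separate set of 500 runs per setting, GP ICC 0.10: 5-7% when the GP effect is already present at baseline, but about 11% when GP effects independent of baseline are combined with recruitment windows or phase-specific effects.

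**Testing the remedy.** In that last set, a GP intercept plus a GP-by-phase term gave 4-6% in every setting, at almost no cost when the GP ICC was 0.

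**The case against.** The strongest reply is that the randomised unit is already in the model. GPs cross over with their municipality, so a stable GP effect largely cancels in the within-municipality comparison, and the municipality term carries part of the rest. This stands. It is why the first block of the table shows little inflation.

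Second, a z test with six clusters is already slightly liberal without any GP correlation (0.050 to 0.068 across the runs), so rates of 6-7% cannot be laid at the door of the missing level. This also stands.

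Third, the planned baseline adjustment can absorb GP differences, because baseline is measured shortly after the GP consultation. It does so when the GP effect is the same at baseline and follow-up, but not when it arises later.

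Fourth, a plain GP intercept does not cure the phase-specific case with period terms (0.098 against 0.102). That is correct, and it is why the GP-by-phase term is needed. Retaining that term only if its variance looks non-zero would be data-driven, so it should be included in advance.

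Fifth, 26 GPs is a target, and physiotherapists who deliver education and exercise are a further possible level. Both are fair limits on the figures.

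A reader might infer that the primary test is simply too liberal. The article does not support that: it gives no GP-level ICC, no recruitment pattern by GP and no measure of varying response. Nor does it present the 0.01 as a provider-level figure, since it says that counties were the clusters.

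**Conclusion.** The point holds in conditional form. The stated model omits a level through which patients are recruited and part of the intervention is delivered, and the attendance covariate does not replace it. Whether the test is distorted depends on three things that the article does not give: the GP-level ICC, how evenly each GP recruits across phases, and how much GPs differ in response after baseline.

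The ranges in the table apply to an assumed GP ICC of 0.05-0.10. Single cells at 0.05 with period terms lie nearer 8%. The simulations also assume the number of periods, the split of GPs between municipalities and one outcome per patient. This is a cheap improvement to a stated rule, not evidence that the primary analysis is invalid.

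**What to change.** Under Statistical analyses, prespecify GP nested in municipality as a random intercept, together with a GP-by-phase random term. Include both whatever their estimated variances, and drop the GP-by-phase term only if the model does not converge. Base the test on a small-sample degrees-of-freedom correction such as Kenward-Roger or Satterthwaite, and report the GP-level ICC.

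The cost is analysis wording. The recruiting GP should already be on record, because contact details reach the project group from the GP's practice. The confidence interval may be slightly wider, and with about 26 GPs some variance estimates may fall on the zero boundary. Data collection was still under way when the article was written, so the change could be fixed before analysis.

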### The primary outcome measure

The participants with hip and/or knee OA will self-report the primary outcome measure, as well as most secondary outcome measures, at five time points: baseline (shortly after the GP consultation) and then 3-monthly (Table 3). The primary outcome will be patient-reported quality of OA care as measured by the OsteoArthritis Quality Indicator questionnaire, a 17-item questionnaire that includes quality indicators (QIs) related to OA patient education and information, regular provider assessments, referrals, and pharmacological treatment [20]. The items were developed from a literature review of published QIs, expert panels, and patient interviews. The patient self-report questionnaire covers one A4 page with yes/no and ‘not applicable’/‘don’t remember’ as response options, and a previous application has showed acceptable validity and reliability in an OA cohort [20]. The total QI pass rate for each person will be calculated as the total number of QIs they passed, divided by the total number of QIs for which they were eligible. At inclusion, the primary outcome measure may be used to assess the effect of the intervention of the GP consultation, whereas at follow-up, it may be used to assess the total effect of the new model.

**Table 3 Tab3:** Primary and secondary outcomes

	Measurement scale	Time^a^
Primary outcome measure (patient-reported)		
OsteoArthritis Quality Indicator Questionnaire [20]	0–100 % (pass rate)	0, 3, 6, 9,12
Patient-reported secondary outcome measures		
Pain level in hip/knee past week	NRS 0–10	0, 3, 6, 9,12
Stiffness in the hip/knee past week	NRS 0–10	---“---
Hip/knee function in the past week	NRS 0–10	---“---
Patient global assessment of the OA disease	NRS 0–10	---“---
Patient acceptable symptom state (PASS)	Acceptable/unacceptable	---“---
Function (Knee injury and Osteoarthritis Outcome Score OoL subscale [44]/Hip disability and Osteoarthritis Outcome Score OoL subscale [45] (K/HOOS)	4 items, 5-point scale	---“---
Physical activity (frequency, intensity, duration) [47]	3 items	---“---
Daily hours in sitting position	1 item	---“---
Satisfaction with the care provided (from patient experience questionnaires [48])	1 item, 5-point scale	---“---
Health related quality of life (EQ-5D) [49]	5 items, 5-point scale	---“---
Body weight	kg	---“---
Health care use past 3 months		---“---
Patient Specific Functional Scale [43]	NRS 0–10	Pre- and post exercise programme
Adverse events	1 item	Exercise diary

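### The CACE estimate is called unbiased, but for the OA-QI the compliance definition leaves allocation other routes to the score, so the label is wrong as written

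*Protocol article*

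**What the plan says.** The primary analysis is intention to treat on the OA-QI pass rate at 6 months. A supportive analysis follows in the same section of the protocol article (Statistical analyses): "A CACE analysis will be performed to provide an unbiased estimate of treatment effect for participants treated as per protocol specification". Being treated per protocol is defined, for those allocated to SAMBA, as "participants having attended the OA patient education programme and performed an exercise programme for at least 8 weeks". No condition is attached to *unbiased*, and the sentence names neither the outcome nor the estimator.

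Four other places bear on it:

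- The section on the intervention phase describes three stages: a first GP consultation, the physiotherapist programme, and a GP review consultation. Table 1 adds GP workshops, outreach visits, reminders, and a check-list of recommended care sent to patients with the 3-month questionnaire.
- The section on the control phase withholds the education programme, booklet, diary and other SAMBA activities from control participants until 12 months after baseline.
- The section on the primary outcome measure says that the OA-QI scores information, provider assessments, referrals and drug treatment. It also says: "At inclusion, the primary outcome measure may be used to assess the effect of the intervention of the GP consultation".
- Baseline is recorded soon after that consultation, and the regression models include the baseline value of the outcome.

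**The concern.** A standard CACE attributes the whole effect of allocation to those who complied. This is valid only under the exclusion restriction: allocation must leave the outcome of non-compliers unchanged. Here, compliance is defined by one part of the package, while the OA-QI scores care delivered by all of it. A participant who completes 7 weeks of exercise is a non-complier, yet may have attended the education, received the booklet, been referred, and been seen by a trained GP. Each of these can turn an OA-QI item from fail to pass.

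At stake is how the result is read. It would be presented as the effect of the model in people treated as intended, with a stated property that the analysis does not have.

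**Working it through.** **Routes from allocation to the OA-QI in non-compliers**

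- *Trained-GP care and GP review.* Neither is described as depending on 8 weeks of exercise. The review comes after baseline.
- *Check-list at 3 months.* It is sent with a questionnaire, before the 6-month time point.
- *Partial physiotherapy attendance.* Education, booklet or referral may be received without 8 weeks of exercise. The booklet comes from the physiotherapist, so it reaches only those who get that far.
- *First GP consultation.* It precedes baseline and is treated separately below.

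**The plan's own figure.** The sample size gives a scale for the effect. Inputs from Sample size calculations: "achieves 80 % power to detect a 10-unit difference between the group means of the primary outcome measure", "when the standard deviation for the primary outcome measure is 24 units", "the drop-out rate is 30 %, and the intraclass correlation is 0.01", "with an average of 50 individuals per cluster", and "using a two-sided test with a significance level of 0.05".

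- Per group before inflation: 2 × [24 × (1.960 + 0.842)/10]² = 90.4, rounded up to 91.
- Design effect: 1 + 49 × 0.01 = 1.49, and 91 × 1.49 = 135.6.
- Drop-out: 135.6/0.70 = 193.7, rounded up to 194.

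The stated 194 per group reproduces and is not in dispute. The 10 units are a difference between group means; below, 10 is borrowed as an illustrative complier effect.

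**Bias of the standard CACE.** Let p be the compliance proportion, c the effect in compliers and g the effect in non-compliers. Controls have no access to the programme, so there are no always-takers by design.

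- ITT = p·c + (1−p)·g
- CACE = ITT/p = c + g(1−p)/p
- Bias = g(1−p)/p

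The documents give neither p nor g, so every value here is an assumption. With c = 10, the estimate is:

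| p | g = −2 | g = 0 | g = 2 | g = 4 |
|---|---|---|---|---|
| 0.8 | 9.5 | 10 | 10.5 | 11.0 |
| 0.6 | 8.7 | 10 | 11.3 | 12.7 |
| 0.4 | 7.0 | 10 | 13.0 | 16.0 |

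Example: p = 0.6 and g = 4 give ITT = 6.0 + 1.6 = 7.6, and 7.6/0.6 = 12.7. A simulation with these values returned 7.6 and 12.7.

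**Effect of the baseline adjustment.** Suppose that g arises wholly at the first GP consultation, is the same in everyone, and is already in the baseline score. With b the slope on baseline, the adjusted ITT is p·c + (1−p)·g − b·g.

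- Against the total complier effect c, the bias is [(1−p) − b]·g/p. At p = 0.6, b = 0.5, g = 4 it is (0.4 − 0.5) × 4/0.6 = −0.7.
- Against the complier effect net of baseline, c − b·g, the bias is (1−b)·g(1−p)/p. At the same values it is 0.5 × 4 × 0.4/0.6 = +1.3.

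So the sign can depend on which complier effect is meant. Effects that arise after baseline are not absorbed, and for them g(1−p)/p stands.

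**The case against.** The case on the other side has several parts.

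- **Baseline adjustment.** A reader might infer that the CACE necessarily overstates the result, and cite the remark about the GP consultation as proof. The documents do not support that. The remark concerns the score at inclusion, and that score is a covariate. Part of the first consultation's effect is removed, and against the total complier effect the net bias can be negative. This stands. It removes certainty about direction, but does not make the estimate unbiased.
- **Outcome and estimator are not named.** A full analysis plan may specify both. This stands as a limit: the point applies to an exclusion-based CACE on the OA-QI. For pain, function or activity, where the effect runs mainly through exercise, the definition is more defensible. But the article asserts the property without condition, and that assertion can be judged as it is.
- **GP workshop attendance is a covariate.** It bears on the GP route, but attendance is itself part of the intervention. Adjusting for it does not restore the exclusion restriction.
- **Size.** From the sample-size inputs, the ITT standard error is about 24 × √(2/91) = 3.6, ignoring the stepped-wedge time structure. The CACE standard error is about 3.6/p. At p = 0.5 and g = 4, the bias of 4.0 compares with a standard error of about 7.1, or 0.6 standard errors. The bias may well be smaller than the sampling error. That tempers the point, but imprecision does not justify the label.
- **Supportive role.** The primary analysis is intention to treat. This is correct and limits the consequence.

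**Conclusion.** Wrong as written. By the article's own description, allocation can change the OA-QI of participants counted as non-compliers. The exclusion restriction behind a standard CACE is therefore not met for that outcome, and the claim of no bias is unsupported.

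For effects that arise after baseline, the bias is g(1−p)/p. It is zero only if g = 0 or everyone complies, and upward if g is positive, as the trial's first hypothesis would suggest. With c = 10, assumed p from 0.8 to 0.4 and assumed g from 0 to 4, the bias is 0 to +6 points. These figures are illustrations and predict nothing about this trial. A firm claim of inflation would go too far, because neither p nor g is documented and baseline adjustment can offset part of the bias. The primary estimate, its test and the sample size are untouched.

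**What to change.** 1. Delete *unbiased*. State that the CACE relies on the exclusion restriction, and name the outcomes to which it is applied.
2. For the OA-QI, report the CACE with a sensitivity range: ITT/p − g(1−p)/p over a stated range of g that includes zero. With ITT = 7.6 and p = 0.6, this gives 12.7 at g = 0, 11.3 at g = 2 and 10.0 at g = 4. Define g on the same baseline-adjusted scale as the ITT estimate, and say that the result is then the complier effect net of what was already present at baseline.
3. Give the education-plus-8-weeks CACE more weight for pain, function and activity.

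Redefining compliance as receipt of any component is not a good substitute. Participants are recruited when they visit their GP, so p would approach 1 and the CACE would approach the ITT. That answers a different question.

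The cost is a wording change and a short calculation. Attendance at education and exercise sessions is already registered (Secondary outcome measures), so no new data are needed.
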